### **4.3 Dose Delay and/or Dose Reduction**

#### **4.3.1 Dose interruption**

Treatment may be interrupted for up to 2 weeks (14 days) to allow study drug-related toxicity to recover to baseline or Grade  $\leq 1$ . For non-treatment-related or unexpected toxicity, whether to discontinue treatment should be decided after discussion between the investigator and the sponsor. If HQP1351 is discontinued for more than 2 weeks (14 days), the subject will be withdrawn from the study. The subject can stay in the study to receive low-dose HQP1351 treatment (determined upon discussion by the principal investigator and the sponsor) if it is considered that the subject can benefit from continuous study treatment.

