#### **3.3.1 Termination of study treatment**

The causes for subjects' discontinuation of study treatment may include:

- AE;
- Lost to follow-up;
- Death;
- Subjects with poor compliance are not suitable for continuing the study, as judged by the

[figure not shown]

investigator.

- The subject withdraws the ICF;
- New anticancer treatment is started;
- Termination of the study by the sponsor;
- PD;
- Others (e.g., the subject can no longer benefit from the study treatment when continuing the study at the discretion of investigator).

For subjects terminating study treatment, see Sections 7.6 and 7.7 for treatment termination and follow-up procedures. For subjects who terminate study treatment due to AEs, investigators will follow up them until the AEs are resolved or stable.

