### **3.3.2 Withdrawal from the Study**

All follow-up procedures will be stopped if a subject withdraws from the study. Reasons for withdrawal from the study may include:

- Death;
- Lost to follow-up;
- The subject withdraws the ICF for participation in the study (including follow-up period);
- The sponsor terminates the study.

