## 4.2 Intolerable Toxicity

Intolerable toxicity is defined as:

- An AE that may affect the subject's ability to continue study-specific procedures or is not in the subject's best interest, at the discretion of the investigator or the Sponsor.
- Toxicity requiring more than twice dose reductions of HQP1351.
- HQP1351 allergy and serious allergic reactions (e.g., hypotension, bronchospasm, and/or rash generalised/erythema).

Subjects who experience intolerable toxicity will permanently discontinue the study unless it is in the subject's best interest to continue the study after the investigator has evaluated the subject's risks and benefits and discussed with the Sponsor.

[figure not shown]

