#### **4.3.2 Dose adjustment**

AEs that occur during this study will be graded according to National Cancer Institute-Common Terminology Criteria for Adverse Events (NCI-CTCAE) (v4.03). According to the correlation of AEs with the study drug and grade, the investigator will take different actions with the study drug, including maintaining the original treatment regimen, withholding dosing, reducing the dose, and terminating the treatment. Up to twice dose reductions are allowed, each to the next lower dose already explored. Any adult subject requiring a reduction of HQP1351 dose below 30 mg QOD should permanently discontinue the study treatment. The study drug can be resumed when the study drug-related toxicities resolve to grade 1 or below.

Dose adjustment may not be performed for grade 1/2 toxicities related to the study drug that can be treated by supportive treatment or don't influence normal daily activities of subjects, unless QTc prolongation, clinically significant pancreatitis, or other clinical conditions that affect subject's safety at the investigator's discretion. For intolerable (symptomatic or influencing subject's normal daily activities) or persistent (unable to be handled with the best supportive care and recovered to grade 1 or baseline after up to 2-week of drug withdrawal) grade 1/2 toxicities related to the investigational product, whether to make dose adjustment will be determined by discussion between the PI and the sponsor.

If a subject experiences grade 3 or 4 investigational drug-related toxicities, the investigational drug should be interrupted immediately. A maximum of 2 weeks (14 days) of drug interruption is permitted to resolve toxicities to Grade 1 or below, or baseline level. The investigational drug can be resumed when the toxicities resolve to Grade 1 or below, or baseline level. Each subject may undergo a maximum of twice dose reductions throughout the study period, and dose increases are generally no longer allowed after dose reductions. Please refer to Table 2-4 for guidance on dose adjustment for study drug-related toxicity.

[figure not shown]**Table 2: Dose delay and adjustment due to hematologic toxicities**

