|                            | 4. If Grade 2 or 3 toxicity recurs after two dose reductions, stop HQP1351 administration, and follow up according to the protocol. |
| Grade 4                    | Stop HQP1351 administration, and follow up according to the protocol.                                                               |

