### **6.3 Prohibited Medications and Therapies**

Patients should be treated according to clinical indications meeting medical standards and at the investigator's discretion. However, the following concomitant medications and therapies are not allowed:

- Surgery;
- Other anti-cancer therapies, including but not limited to: chemotherapeutic agents, immunotherapy (such as vaccines), biological response modifiers, radiotherapy, and/or systemic hormone therapy.
- Immune support drugs, except for 4 weeks before the first planned dose of the investigational drug, a stable dose of corticosteroids may be used.
- Traditional Chinese medicine claimed to have anti-tumor activity;
- Other medications that should be prohibited at the investigator's discretion.

If the subject's clinical condition requires a prohibited medication or treatment, the investigational drug should be discontinued and the subject should withdraw from the trial.

[figure not shown]

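### Sections 4.3.1 and 6.3 withdraw subjects from the study or trial, which under 3.3.2 ends all follow-up, while the follow-up rules keep such subjects under scans and survival contact (minor)

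*Protocol*

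**What the plan says.** Protocol section 3.3 sets up two exits with different consequences.

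- **Stopping treatment (3.3.1).** Listed reasons include adverse event, progression and the start of a new anticancer treatment. Follow-up goes on: "For subjects terminating study treatment, see Sections 7.6 and 7.7 for treatment termination and follow-up procedures".
- **Leaving the study (3.3.2).** "All follow-up procedures will be stopped if a subject withdraws from the study". The listed reasons are death, loss to follow-up, withdrawal of consent and termination by the sponsor. The list is introduced as open.

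Two operational rules use the language of the second exit.

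- **4.3.1:** "If HQP1351 is discontinued for more than 2 weeks (14 days), the subject will be withdrawn from the study". There is one exception, for expected benefit: "The subject can stay in the study to receive low-dose HQP1351 treatment".
- **6.3:** if the subject's condition requires a prohibited medication or treatment, "the investigational drug should be discontinued and the subject should withdraw from the trial". There is no exception.

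A third rule is worded similarly. Section 4.2 states: "Subjects who experience intolerable toxicity will permanently discontinue the study unless it is in the subject's best interest".

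The follow-up rules, on the other hand, run on after the drug is stopped. Section 7.7.2.1 has tumor assessment every 8 weeks until objective progression or other antitumor therapy. Section 8 and Schedule footnote 15 repeat this and exempt only a subject who leaves voluntarily. Section 8.1.10 adds withdrawal of consent as an end point. Section 7.7.2.2 collects survival status every 3 months until death, loss to follow-up or withdrawal of consent.

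**The concern.** A subject who is off drug for 15 days because of toxicity and is not offered a low dose has not progressed, started another therapy or withdrawn consent. Sections 7.7.2, 8 and 8.1.10 keep that subject under follow-up. Sections 4.3.1 and 3.3.2, read together and literally, end it. No sentence says which governs, so sites could act differently on the same event.

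The endpoints at stake are PFS, DOR and OS. Under section 10.2.2 a subject without progression or death is censored for PFS at the last adequate tumor assessment, and DOR uses the same rule. If scans stop because toxicity kept the subject off drug, the censoring is tied to the course of treatment and may be informative. Deaths after the last contact would also be missing from OS. A later analysis plan cannot recover scans and contacts that were never made.

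**Working it through.** There is no figure in the plan to reproduce. The check sets the texts side by side.

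**Step 1. Same event, two outcomes.**

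| Event | Read with 3.3.2 | Read with 3.3.1, 7.7.2, 8, 8.1.10, footnote 15 |
|---|---|---|
| More than 14 days off drug, no low dose (4.3.1) | Scans and survival contact stop | Scans every 8 weeks to progression or other antitumor therapy; survival contact every 3 months |
| Prohibited treatment, not antitumor (6.3) | Scans and survival contact stop | As above |
| Prohibited treatment, antitumor (6.3) | Scans and survival contact stop | Scans end when the new therapy starts; survival contact continues |

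In the third row the two readings differ mainly on survival. Surgery probably belongs there: 6.3 lists it immediately before the other anticancer therapies, and the screening section (7.2.2) counts it among previous antitumor treatments. What is clearly not antitumor in 6.3 is narrow: immune support drugs and medication barred at the investigator's discretion.

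**Step 2. Does the wording of 4.3.1 and 6.3 point to treatment or to the study?** Two things favour the literal reading. Section 4.3.2, immediately after 4.3.1, uses the treatment-level term: "Any adult subject requiring a reduction of HQP1351 dose below 30 mg QOD should permanently discontinue the study treatment". And 6.3 names stopping the drug and leaving the trial as two separate acts, so the second is not naturally a synonym for the first.

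**Step 3. Effect on one subject (illustration on the 8-week schedule).** Suppose the last adequate scan without progression is at week 16, the drug is then stopped under 4.3.1, and the next scan, at week 16 + 8 = 24, would show progression.

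- Literal reading: PFS is censored at week 16, and a later death is not collected.
- Follow-up reading: PFS is an event at week 24, and survival contact continues.

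**Step 4. Which endpoints are reached.** PFS, DOR and OS are secondary (10.2.2). The primary endpoint is safety, and adverse event follow-up is largely secured by other text. Section 3.3.1 follows adverse events that ended treatment until resolved or stable. The opening of section 7 follows grade 3 or 4 laboratory results after withdrawal. Section 9.2.1 collects events to 30 days after the last dose, and 9.2.2 follows all events to outcome or stability. Section 3.3 also asks for the protocol-specified visit after either kind of exit.

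**The case against.** The strongest reply is that the protocol uses these words loosely and that the authors meant stopping treatment. There is real support for this.

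- Section 4.1, on treatment beyond progression, speaks of benefit from continuing the study where continuing the drug is meant.
- Section 4.4 speaks of subjects withdrawn because of progression, although 7.7.2.2 provides survival follow-up after progression.
- Section 7 requires follow-up of laboratory abnormalities present at study withdrawal, which 3.3.2 would forbid if taken strictly.
- Schedule footnote 7 gives a withdrawal label to the visit within 14 days after the last dose.
- The reasons in 3.3.2 include no toxicity, interruption or prohibited medication.
- Section 4.3.1 deals with dose interruption, and its exception contrasts leaving with staying on drug.

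This stands as evidence of likely intent. It does not settle the matter: loose usage is what makes the term ambiguous, the 3.3.2 list is open, 4.3.1 and 6.3 use its withdrawal wording, and no sentence defines the term for them.

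Three stronger inferences are not supported.

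- **That 4.2 also cuts off follow-up.** Its wording matches the section 4.1 usage, and Table 4 directs: "If Grade 2 or 3 toxicity recurs after two dose reductions, stop HQP1351 administration, and follow up according to the protocol". It most naturally means stopping treatment and needs only a wording clean-up.
- **That the 5 of 36 subjects who stopped for adverse events (1.5.2) measure lost follow-up.** Section 3.3.1 sends such subjects to follow-up, and nothing says how many stopped under 4.3.1 or 6.3. Of the 28 subjects with an efficacy assessment, 18 already had progression (1.5), which may further limit the number who could be censored this way. No projection from 5 of 36 is warranted.
- **That safety follow-up is lost.** The texts in step 4 largely protect it.

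**Conclusion.** The inconsistency is real for 4.3.1 and 6.3, and it is minor. A site that follows those two sections literally would end scans and survival contact where the follow-up sections require them. Under 4.3.1 that means early censoring of PFS and DOR, mostly for toxicity-related reasons, and incomplete OS. Under 6.3 it means incomplete OS, with scans also lost where the prohibited treatment is not antitumor.

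The number affected is unknown and cannot be estimated from the protocol. The harm depends on sites reading the text literally; the protocol does not show that any has. The effect is confined to secondary endpoints of a Phase I study whose efficacy aim is preliminary.

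**What to change.** In 4.3.1 and 6.3, state that the subject permanently stops study treatment and continues follow-up under 7.6 and 7.7. Use the same wording in 4.2 for consistency. Keep the existing exceptions: low-dose continuation in 4.3.1 and the subject's best interest in 4.2. Reserve study withdrawal for the reasons given in 3.3.2.

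The cost is a wording amendment. The visits and contacts in 7.6 and 7.7 are already scheduled, so no new procedure is needed.

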#### **4.3.2 Dose adjustment**

AEs that occur during this study will be graded according to National Cancer Institute-Common Terminology Criteria for Adverse Events (NCI-CTCAE) (v4.03). According to the correlation of AEs with the study drug and grade, the investigator will take different actions with the study drug, including maintaining the original treatment regimen, withholding dosing, reducing the dose, and terminating the treatment. Up to twice dose reductions are allowed, each to the next lower dose already explored. Any adult subject requiring a reduction of HQP1351 dose below 30 mg QOD should permanently discontinue the study treatment. The study drug can be resumed when the study drug-related toxicities resolve to grade 1 or below.

Dose adjustment may not be performed for grade 1/2 toxicities related to the study drug that can be treated by supportive treatment or don't influence normal daily activities of subjects, unless QTc prolongation, clinically significant pancreatitis, or other clinical conditions that affect subject's safety at the investigator's discretion. For intolerable (symptomatic or influencing subject's normal daily activities) or persistent (unable to be handled with the best supportive care and recovered to grade 1 or baseline after up to 2-week of drug withdrawal) grade 1/2 toxicities related to the investigational product, whether to make dose adjustment will be determined by discussion between the PI and the sponsor.

If a subject experiences grade 3 or 4 investigational drug-related toxicities, the investigational drug should be interrupted immediately. A maximum of 2 weeks (14 days) of drug interruption is permitted to resolve toxicities to Grade 1 or below, or baseline level. The investigational drug can be resumed when the toxicities resolve to Grade 1 or below, or baseline level. Each subject may undergo a maximum of twice dose reductions throughout the study period, and dose increases are generally no longer allowed after dose reductions. Please refer to Table 2-4 for guidance on dose adjustment for study drug-related toxicity.

[figure not shown]**Table 2: Dose delay and adjustment due to hematologic toxicities**

| Toxicity / NCI-CTCAE grade                                                                                                                                        | Actions to be taken                                                                                                                                                                                                                                                                                                                                                                                                                                                                                                                                                                                                                       |
|-------------------------------------------------------------------------------------------------------------------------------------------------------------------|-------------------------------------------------------------------------------------------------------------------------------------------------------------------------------------------------------------------------------------------------------------------------------------------------------------------------------------------------------------------------------------------------------------------------------------------------------------------------------------------------------------------------------------------------------------------------------------------------------------------------------------------|
| Platelets decreased                                                                                                                                        |                                                                                                                                                                                                                                                                                                                                                                                                                                                                                                                                                                                                                                           |
| Grade 1 ( $\geq 75 \times 10^9/L$ )                                                                                                                               | No dose adjustment required.                                                                                                                                                                                                                                                                                                                                                                                                                                                                                                                                                                                                              |
| Grade 2 ( $\geq 50 \times 10^9/L$ - $< 75 \times 10^9/L$ )                                                                                                        | 
 
1. Interrupt HQP1351 administration until toxicity resolves to Grade <math>\leq 1</math>.
 
2. Restart HQP1351 administration at the original dose level.
 
                                                                                                                                                                                                                                                                                                                                                                                                                        |
| Grade 3 ( $\geq 25 \times 10^9/L$ - $< 50 \times 10^9/L$ )                                                                                                        | 
 
1. Interrupt HQP1351 administration until toxicity resolves to Grade <math>\leq 1</math>.
 
2. Restart HQP1351 administration at the original dose level.
 
3. If Grade 3 toxicity recurs, interrupt HQP1351 administration until toxicity resolves to Grade <math>\leq 1</math>, and restart HQP1351 administration at a reduced dose level.
 
                                                                                                                                                                                                                             |
| Grade 4 ( $< 25 \times 10^9/L$ )                                                                                                                                  | 
 
1. Interrupt HQP1351 administration until toxicity resolves to Grade <math>\leq 1</math>.
 
2. Restart HQP1351 treatment at a reduced dose level.
 
3. If Grade 4 toxicity recurs, stop HQP1351 treatment.
 
                                                                                                                                                                                                                                                                                                                                                                |
| Neutrophils reduced:                                                                                                                                       |                                                                                                                                                                                                                                                                                                                                                                                                                                                                                                                                                                                                                                           |
| Grade 1 ( $\geq 1.5 \times 10^9/L$ )                                                                                                                              | No dose adjustment required.                                                                                                                                                                                                                                                                                                                                                                                                                                                                                                                                                                                                              |
| Grade 2 ( $\geq 1.0$ - $< 1.5 \times 10^9/L$ )                                                                                                                    | No dose adjustment required.                                                                                                                                                                                                                                                                                                                                                                                                                                                                                                                                                                                                              |
| Grade 3 ( $\geq 0.5$ - $< 1.0 \times 10^9/L$ )                                                                                                                    | 
 
1. Interrupt HQP1351 administration until toxicity resolves to <math>\geq 1.0 \times 10^9/L</math>.
 
2. Restart HQP1351 administration at the original dose level.
 
3. If Grade 3 toxicity recurs, interrupt HQP1351 administration until toxicity resolves to <math>\geq 1.0 \times 10^9/L</math>. 
 
a) If the duration is less than or equal to 7 days, resume administration at the original dose level.
 
b) If the duration is greater than 7 days, resume HQP1351 administration at a reduced dose level.
 
 
 
 |
| Grade 4 ( $< 0.5 \times 10^9/L$ )                                                                                                                                 | 
 
1. Interrupt HQP1351 administration until toxicity resolves to <math>\geq 1.0 \times 10^9/L</math>.
 
2. Restart HQP1351 administration at a reduced dose level.
 
3. If Grade 4 toxicity recurs, interrupt HQP1351 administration until toxicity resolves to <math>\geq 1.0 \times 10^9/L</math>, and resume administration at a reduced dose level.
 
4. A maximum of two dose reductions is allowed.
 
                                                                                                                                                            |
| Febrile neutropenia                                                                                                                                        |                                                                                                                                                                                                                                                                                                                                                                                                                                                                                                                                                                                                                                           |
| Grade 3: ANC $< 1.0 \times 10^9/L$ accompanied by single body temperature $> 38.3^\circ\text{C}$ or body temperature $\geq 38^\circ\text{C}$ for more than 1 hour | 
 
1. Interrupt HQP1351 administration until ANC recovers to <math>\geq 1.0 \times 10^9/L</math> and there is no fever.
 
2. Restart HQP1351 administration at a reduced dose level.
 
3. If febrile neutropenia recurs, stop HQP1351 administration.
 
                                                                                                                                                                                                                                                                                                                        |
| Grade 4: life-threatening, urgent intervention indicated                                                                                                          | Stop HQP1351 administration.                                                                                                                                                                                                                                                                                                                                                                                                                                                                                                                                                                                                              |
| Anemia (Hemoglobin)                                                                                                                                        |                                                                                                                                                                                                                                                                                                                                                                                                                                                                                                                                                                                                                                           |

[figure not shown]

| Toxicity / NCI-CTCAE grade                               | Actions to be taken                                                                                                                                                                                                |
|----------------------------------------------------------|--------------------------------------------------------------------------------------------------------------------------------------------------------------------------------------------------------------------|
| Grade 1 ( $\geq 10.0$ - LLN g/dL)                        | No dose adjustment is required.                                                                                                                                                                                    |
| Grade 2 ( $\geq 8.0$ - $<10.0$ g/dL)                     | No dose adjustment is required.                                                                                                                                                                                    |
| Grade 3 ( $<8.0$ g/dL)                                   | 
 
1. Interrupt HQP1351 administration until toxicity resolves to Grade <math>\leq 2</math>.
 
2. Restart HQP1351 administration at the original dose level.
 
 |
| Grade 4: life-threatening, urgent intervention indicated | Stop HQP1351 administration.                                                                                                                                                                                       |

